### 3.2. Pitfalls and Mitigation Strategies

Frequent endovaginal ultrasounds may not be acceptable for the duration of the three cycles of use being requested of participants. To mitigate this, we will use trained ultrasound technologists and a patient-centered approach to provide participants with an acceptable level of discomfort during the procedure. A research assistant will follow up to ensure that ultrasound schedule reminders are provided to avoid missing follicular scans. During recruitment, we will seek subjects who would feel comfortable with this frequency of ultrasounds. We will oversample up to 60 participants, as stated earlier, to ensure we can have 150 cycles for analysis to achieve the appropriate power for our study.

Correlating progesterone changes with temperature and ultrasound-confirmed ovulation will help to validate progesterone as a confirmation of ovulation. Some studies have identified inconsistencies in specific PDG levels in the confirmation of ovulation [54], while other studies with ultrasound-confirmed ovulation have been able to identify relevant PDG levels to confirm ovulation [55].

### 3.3. Anticipated Results

We expect that the Mira monitor will accurately and precisely identify and confirm the day of ovulation as shown on ultrasound. Bleeding patterns and menstrual cycle observations will provide a baseline pattern for normal healthy participants to compare to abnormal cycles. We may be able to further expand on previous work related to daily quantitative hormone patterns, for example, by modelling estrogen changes from follicular wave activity in the early follicular phase [56], demonstrating the diversity of LH profiles related to ovulation patterns [57], or showing luteal progesterone variability [52,58]. The results from this study will potentially provide nomograms for urinary hormone measurements and provide reference values for future studies evaluating menstrual health.

## 4. Discussion

### 4.1. Regulatory Processes

Health Canada provided Investigational Testing Authorization (ITA, Class II) in June 2020 (Application No. 305611) for our pilot study, and an updated ITA has been submitted for the present study (Application No. 360587). The Ethics Board on record will be the Conjoint Health Research Ethics Board (CHREB) at the University of Calgary. This study is registered under clinicaltrials.gov and the record has been released and made public (https://clinicaltrials.gov/study/NCT05936840, accessed on 7 July 2023).

### 4.2. Establishing a Gold Standard for Menstrual Cycle Monitoring

Previous well-planned studies like this one have provided valuable and relevant data for analysis for two decades after their original collection [51,52,55]. We will be building on previous menstrual health research and incorporating new technological and personalized tools (i.e., the Mira monitor, the RYB App) with a focus on validation, privacy, security, and analytic precision. We hope that these tools will empower women to keep track of their menstrual health and identify changes that might provide early warnings for abnormalities in their menstrual cycles. More complex tools like the Mira hormone monitor give women precision and accuracy in planning for conception or for identifying fertility in difficult circumstances (e.g., perimenopause and postpartum). Having other tools that reduce the participant burden such as a thermometer or other wearable temperature sensors validated for menstrual cycle prediction will help athletes and others who want to employ new wearable technologies to monitor menstrual health that are easily incorporated in daily routines. A reliable and private app like the Read Your Body App will provide users with ways to track their cycle accurately without worrying about data breaches.

Participants in the sample with regular cycles or oligomenorrhea will hopefully identify important insights with the urinary hormones and menstrual cycle monitoring to guide decisions about fertility, particularly in the context of PCOS and oligomenorrhea in athletes, since these are relatively hypofertile states. Moreover, knowledge of the menstrual cycle allows people with PCOS to manage the unopposed estrogen long-term (with appropriate treatments to regulate the cycle in PCOS) and thus decrease the overall risk of endometrial cancer. Athletes may want to have easy methods to predict their menstrual cycle patterns to plan training and performance accordingly. Although urine hormone measurements may not be practical for many busy athletes, if we are able to precisely correlate hormone findings with vital signs, wearable biosensor technology may help to identify their menstrual cycle changes.

### 4.3. Economic Benefit

The validation of the Mira monitor for tracking the health of the menstrual cycle could have significant economic benefits for individuals and the health system as a whole.

Follicular tracking ultrasound for the purposes of identifying a healthy ovulation pattern can be expensive. There are usually 3–6 ultrasounds as part of the protocol, and considering the time for an ultrasound technician to perform the scan and a radiologist to review the scan, the cost per scan is likely around CAD 50–80, which would be CAD 150–480 per cycle.

Serum hormone tests are approximately CAD 15 per assay for estrogen, progesterone, FSH, and LH. If this were done 2–3 times per cycle (e.g., early follicular, peri-ovulatory, mid-luteal), this would cost CAD 180 per cycle. By contrast, the Mira monitor has an upfront cost of CAD 250, with a monthly cost of CAD 25–60 per cycle for test sticks that are CAD 3–4 each. Since the Mira monitor can be used for several years, the monthly cost to use the monitor would be one-third of the cost of serum measurements (which would be fewer in number), and it is even more economical compared to follicular tracking ultrasound.

The other important consideration of this economic benefit is that the Mira monitor is used at home, with no cost for travel nor for in-person visits to a provider to obtain requisitions. Moreover, the Mira monitor provides data about day-to-day changes to show hormonal variability across the menstrual cycle, rather than providing only three days of values (in the case of serum measurements) or a single day identified as ovulatory (in the case of follicular tracking).

Validating this at-home urine monitoring tool for the sake of menstrual cycle literacy, and to track abnormalities or to help with fertility, would provide dramatic savings to the health care system as a whole. This is especially the case because if women are tracking on their own, they would be paying for the Mira monitor and test sticks out of pocket, sometimes covered by a health spending account with their private insurance. This would relieve the burden of having to see a physician, obtain requisitions, and go to the lab or diagnostic imaging facility to obtain the required tests. For 100 women tracking 12 menstrual cycles over 1 year, this would amount to saving CAD 216,000 in lab costs and CAD 378,000 in ultrasound costs for the health care system.

### 4.4. Future Directions

Precision monitoring of the menstrual cycle is expected to impact many women who want to increase their menstrual health literacy for health benefits. Once the ultrasound validation is complete, tools like the Mira monitor can be relied upon for tracking medical treatments for various conditions without having to include the gold standard of ultrasound in every study. In the future, dynamic daily urine hormone measurements may replace serum hormone evaluation of the menstrual cycle. These tools may also form part of adverse health outcomes monitoring, including gynecologic cancer prediction models.

In this context, with these validated menstrual cycle monitoring tools, future studies could evaluate other gynecologic states. In endometriosis, shorter and heavier menstrual cycles have been associated with an increased risk of endometriosis [59]. The mechanism of the shorter menstrual cycles is not known, but it may be hypothesized that luteal progesterone may play a role given that there is evidence of progesterone-receptor resistance in the endometrium of patients with endometriosis [60]. Being able to identify urinary progesterone correlates could help establish the mechanism of the short cycles in endometriosis. Menstrual cycle monitoring may be able to recognize abnormal bleeding patterns and other possible subtle variations in their menstrual cycle that may relate to endometriosis-associated subfertility.

Finally, women approaching their decline of fertility in perimenopause may have abnormal bleeding and menstrual cycle patterns. While these patterns may be part of the normal transition to menopause, for example with more frequent anovulation [61], it is also possible they reflect abnormal hormone patterns leading to endometrial hyperplasia. Urine hormone monitoring at this stage in life may contribute to predicting endometrial hyperplasia and identify those at risk of later development of endometrial cancer.

## Figures and Tables

**Figure 1 medicina-59-01513-f001:**
[figure not shown]
Ovarian–uterine (menstrual) cycle. (**A**) The hypothalamic–pituitary–ovarian (HPO) axis involves hormonal feedback loops between the ovaries, the hypothalamus, and the pituitary, which regulate the reproductive hormones and ovulation (**B**). A cycle begins with menses (**C**), the shedding of the endometrial lining (**D**), while follicle development is stimulated by FSH and estrogen (E_1_3G) to select a dominant follicle, which ruptures to release an egg under the stimulation of the LH surge (**F**). Progesterone rises after ovulation, which causes a basal body temperature shift (**E**) and supports the lining of the uterus (endometrium, (**D**)) to facilitate implantation of an embryo. If no embryo implants, progesterone falls (**F**), leading to menses (**C**). The follicular phase is from menses until ovulation, and the luteal phase is from ovulation until the end of the cycle (**G**). Adapted by [name] with permission from SERVIER Medical Art (smart.servier.com, accessed on 1 October 2022).

**Figure 2 medicina-59-01513-f002:**
[figure not shown]
**Figure 2**. (**A**)—Mira Analyzer diagram from manufacturer (used with permission). (**B**)—Mira test stick lateral flow assay (**A**), based on a double antibody fluorescent labeling technique. LH and FSH are based on a sandwich assay and E_1_3G and PDG are based on a competition assay (**B**). For the sandwich assay, anti-LH or anti-FSH capture antibodies bind to LH and FSH in the urine and are bound to immobilized anti-LH and anti-FSH in the detection zone (as more hormone is present, there is a greater detection and stronger line intensity to be detected by the signal receiver). For the competition assay, E_1_3G and PDG in the urine compete with an immobilized binding antigen of these hormones, so if there is more hormone present, there is less binding and therefore a lower line intensity to be detected by the receiver (**A**). Adapted by [name] with permission from Radetech www.lateralflows.com/lateral-flow-assays/ accessed on 1 March 2023.

**Figure 3 medicina-59-01513-f003:**
[figure not shown]
Data collection process for the study. Mira monitor urine results and other menstrual cycle observations are recorded in the Read Your Body (RYB) App. Users collect, control, and own the data they collect. RYB data is stored locally. Participants can then voluntarily send their anonymous data to a REDCap research database. Component figures used with permission.

**Table 1 medicina-59-01513-t001:** Inclusion and exclusion criteria for regular cycles.

Inclusion Criteria	Exclusion Criteria
Regularly menstruating participants aged 18–45 Consistent cycle lengths between 24–38 days Knowledge of previous 3 cycle lengths Negative pregnancy test at the beginning and at the end of each cycle Able to travel to clinic in Calgary for regular ultrasounds during the study period	Anovulation in the last 3 cycles Currently, or in the previous 3 months, on medications that are known to impair or stimulate ovulation (e.g., oral contraceptives, ovulation stimulants, etc.) Known conditions that impair ovulation or fertility: ▪ polycystic ovarian syndrome ▪ endometriosis ▪ pelvic inflammatory disease in the last year ▪ pituitary adenoma ▪ breastfeeding Previous surgeries impacting the menstrual cycle: ▪ hysterectomy ▪ bilateral oophorectomy Currently pregnant

**Table 2 medicina-59-01513-t002:** Inclusion and exclusion criteria for oligomenorrheic cycles.

Inclusion Criteria	Exclusion Criteria
Participants aged 18–45 With a clinical diagnosis of PCOS (Rotterdam criteria [45] to include oligomenorrheic cycles and one of either polycystic ovaries or signs of excess androgens) OR Oligomenorrheic athletes	Currently, or in the previous 3 months, on medications that are known to impair or stimulate ovulation (e.g., oral contraceptives, ovulation stimulants, etc.) Known conditions that impair ovulation or fertility: ▪ pelvic inflammatory disease in the last year ▪ pituitary adenoma ▪ breastfeeding Previous surgeries impacting the menstrual cycle: ▪ hysterectomy ▪ bilateral oophorectomy Currently pregnant

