## Abstract

*Background and Objectives*: The Quantum Menstrual Health Monitoring Study will measure four key reproductive hormones in the urine (follicle-stimulating hormone, FSH; estrone-3-glucuronide, E_1_3G; luteinizing hormone, LH; and pregnanediol glucuronide, PDG) to characterize patterns that predict and confirm ovulation, referenced to serum hormones and the gold standard of the ultrasound day of ovulation in participants with regular cycles. These normal cycles will provide a reference for comparison to irregular cycles in subjects with polycystic ovarian syndrome (PCOS) and athletes. *Materials and Methods*: Participants will track their menstrual cycles for 3 months and be provided with an at-home urine hormone monitor (Mira monitor) to predict ovulation. The day of ovulation will be confirmed with serial ultrasounds completed in a community clinic. Urine results will be compared to serum hormone values. Other markers of menstrual health, such as bleeding patterns and temperature changes, will be determined using a customized app. Three groups will be recruited. Group 1 will include those with consistent regular cycle lengths (between 24–38 days), and will be compared to two groups with irregular cycle lengths (with increased cycle length variability and longer cycles). Group 2 will include those with polycystic ovarian syndrome (PCOS) with irregular cycles and Group 3 will include individuals participating in high levels of exercise with irregular cycles. *Hypothesis*: The Mira monitor quantitative urine hormone pattern will accurately correlate with serum hormonal levels and will predict (with LH) and confirm (with PDG) the ultrasound day of ovulation in those with regular cycles as well as those with irregular cycles. *Rationale*: Once the ultrasound validation is complete, tools like the Mira monitor with a customized app may become a new standard for at-home and remote clinical monitoring of the menstrual cycle without having to use labor-intensive follicular-tracking ultrasound or follow serum hormone changes. *Conclusions*: Precision monitoring of the menstrual cycle is expected to impact individuals who want to increase their menstrual health literacy and guide decisions about fertility.

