### 2.3. Inclusion and Exclusion Criteria

Purposive sampling will be carried out to ensure an ethnically diverse sample reflective of the Canadian population. Table 1 and Table 2 outline the inclusion and exclusion criteria. These participants will be recruited through primary care clinics and university social media advertising along with snowball sampling in the community. Irregular cycles in PCOS will be identified based on historical cycle lengths and variability as well as one other Rotterdam criterion (Table 2). Irregular cycles in athletes will also be identified based on historical cycle lengths and variability, specifically when an athlete has recognized less frequent cycles with their training activities. Athletes will be recruited from known sports research groups locally.

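### Tables 1 and 2 apply unequal eligibility rules to groups that will be compared: Table 2 has no rule for athletes who also meet the PCOS definition, no endometriosis exclusion and no per-cycle pregnancy test

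*Protocol article*

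**What the plan says.** The Abstract separates the irregular groups by cause: "Group 2 will include those with polycystic ovarian syndrome (PCOS) with irregular cycles and Group 3 will include individuals participating in high levels of exercise", also with irregular cycles. Section 2.1 plans to compare the regular-cycle group with each of them.

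Table 2 is a single list for both irregular groups. Its PCOS branch needs a clinical diagnosis, and the athlete branch is joined to it by a plain OR: "one of either polycystic ovaries or signs of excess androgens) OR Oligomenorrheic athletes". Section 2.3 adds that athletes are identified from historical cycle length and variability, "specifically when an athlete has recognized less frequent cycles with their training activities".

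For Group 1, Table 1 excludes named conditions that include "polycystic ovarian syndrome ▪ endometriosis ▪ pelvic inflammatory disease in the last year". The matching entry in Table 2 reads "Known conditions that impair ovulation or fertility: ▪ pelvic inflammatory disease in the last year ▪ pituitary adenoma ▪ breastfeeding". Table 1 also requires a "Negative pregnancy test at the beginning and at the end of each cycle". Table 2 has no such item. Both tables exclude women who are currently pregnant.

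**The concern.** When groups are to be compared, the eligibility rules should differ only in what defines the groups. Here they differ in three further ways.

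- **Overlap.** The PCOS exclusion had to be dropped for Group 2, but it was not restored for athletes. An oligomenorrheic athlete with polycystic ovaries or androgen excess can satisfy both branches. The article treats the two states as separate in meaning: section 4.2 ties PCOS to unopposed estrogen and endometrial cancer risk, and athletes to training and performance. If some of Group 3 have PCOS, a difference from Group 1 cannot be attributed cleanly to exercise.
- **Endometriosis.** It is excluded on one side of each comparison with Group 1 and allowed on the other. Section 4.4 says that "shorter and heavier menstrual cycles have been associated with an increased risk of endometriosis", and section 3.1 reports cycle length and bleeding scores.
- **Pregnancy.** Listing a per-cycle test beside the exclusion of current pregnancy implies that the exclusion alone was not thought enough for Group 1. Table 2 keeps only the exclusion, in the groups where a late period tells least. Recent oral-contraceptive users are excluded from these groups too, so conception during follow-up is plausible.

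Section 3.3 hopes for nomograms and reference values, so a misassigned participant or a conception cycle could carry forward into later use.

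**Working it through.** **1. The plan's own figure.** Section 2.4 gives effect size 0.2, alpha 0.05, one tail, 80% power and 150 cycles.

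- Point-biserial correlation model (noncentral t, N − 2 degrees of freedom, noncentrality 0.2/√(1 − 0.04) × √N): the smallest N with at least 80% power is 150, which matches.
- Fisher z: ((1.645 + 0.842)/atanh(0.2))² + 3 = 153.4, so 154. Power at 150 is 79.2%.

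Nothing below changes this number.

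**2. The two tables side by side.**

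| Item | Table 1 (Group 1) | Table 2 (Groups 2 and 3) |
|---|---|---|
| PCOS | Excluded | Defines Group 2; not excluded for athletes |
| Endometriosis | Excluded | Not listed |
| Pelvic inflammatory disease in the last year, pituitary adenoma, breastfeeding | Excluded | Excluded |
| Currently pregnant | Excluded | Excluded |
| Negative pregnancy test at start and end of each cycle | Required | Not listed |
| Rule for meeting both definitions | Not applicable | None |

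The training-related history in section 2.3 narrows the overlap but does not rule out PCOS.

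**3. Overlap in the planned contrast.** Let q be the share of Group 3 who also have PCOS, E the difference from Group 1 for athletes without PCOS, and P the difference for athletes with it. The observed difference between Group 3 and Group 1 is (1 − q)E + qP, so it departs from E by q(P − E). The documents give none of q, E or P, so no figure in days follows. For scale only, with q assumed at 5–30%, 0.05 × 50 = 2.5 to 0.30 × 50 = 15 participants would be involved, or 7.5 to 45 of 150 cycles.

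**4. Undetected conceptions.** If a share c of cycles is lengthened by L days, the mean cycle length rises by c × L. Both inputs are assumptions.

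| c | Cycles of 150 | L = 7 | L = 14 | L = 28 |
|---|---|---|---|---|
| 1% | 1.5 | 0.07 d | 0.14 d | 0.28 d |
| 2% | 3 | 0.14 d | 0.28 d | 0.56 d |
| 5% | 7.5 | 0.35 d | 0.70 d | 1.40 d |

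Section 2.4 states a detectable difference of 0.5 days and names cycle length among the quantities it covers. The Figure 1 legend runs the luteal phase from ovulation to the end of the cycle, so the added days fall in that phase.

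**5. Endometriosis.** The documents give no prevalence and no effect in days, so only the direction can be read: shorter, heavier cycles.

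**The case against.** - **The powered analysis is hardly touched.** Section 3.1 makes the main analysis a Spearman correlation of the ultrasound day of ovulation with the LH peak and the progesterone rise. The cause of oligomenorrhea does not change that reference standard, and a conception cycle still supplies an ovulation day, an LH peak and a PDG rise. This stands; what remains at risk is the group comparisons and descriptive summaries.
- **Overlap does not shrink a planned contrast.** A reader might infer that the Group 2 versus Group 3 difference is diluted by the factor 1 − q. No such test is planned; both stated comparisons are with Group 1. The harm is to attribution.
- **The overlap is narrow.** Group 2 needs a clinical diagnosis, and athletes come from sports research groups with a training-related history. That reduces the overlap but still assigns nobody who meets both definitions.
- **Endometriosis is weak ground.** A reader might infer that both contrasts are confounded. Section 4.4 reports an association with shorter cycles, only hypothesises a role for luteal progesterone, and refers to receptor resistance that this study does not measure. The general wording above the Table 2 list might be thought to cover endometriosis, but the list names specific conditions and omits this one.
- **Pregnancy may be an editorial omission.** Table 2 also drops the travel requirement, although all scans are in one Calgary clinic. A reader might infer that Table 2 screens for pregnancy only at entry, but it does not say so. An ongoing conception would not end in menses, and daily PDG with 6–8 scans per cycle may reveal some. The realistic exposure is early losses, not very long conception episodes.
- **The shift is small beside the contrast.** With an assumed irregular-group mean of 45 days and the 31-day midpoint of 24–38, the gap is 14 days. A shift of 0.14–0.70 days is 1–5% of that and cannot reverse it. This stands.

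**Conclusion.** The unequal rules are on the page. Both tables are printed as full criteria lists, and followed as written they give groups that are less comparable than intended; this is more than detail left to a longer document.

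Three consequences are possible rather than certain. In order of strength:

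1. A difference between Group 1 and athletes may partly reflect PCOS.
2. Early pregnancy losses may be counted as long cycles in the cycle-length, luteal-phase and PDG summaries.
3. The contrasts with Group 1 may be unequal on endometriosis.

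The size cannot be derived from the documents. The shift of 0.14–0.70 days in mean cycle length rests wholly on the assumed 1–5% of cycles and 14 added days. It is of the order of the 0.5 days in section 2.4, but that comparison gives scale only and does not show a loss of power. The documents do not support any claim that the ovulation-day validation or the 150-cycle calculation fails.

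**What to change.** - Reconcile Table 2 with Table 1: add endometriosis to the exclusions, require the same pregnancy test at the start and end of each cycle, and handle conception cycles by one stated rule in all three groups.
- State which group a participant belongs to when she meets both the PCOS and the athlete definition.
- Flag athletes who meet the Rotterdam definition already in Table 2, using the ultrasounds already planned, and report Group 1 versus Group 3 with and without them.

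The cost is a few urine pregnancy tests, slightly narrower eligibility and one extra sensitivity analysis.

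Removing flagged athletes from the main Group 3 contrast is not needed. With an assumed 10–30% flagged, keeping 50 would mean recruiting 50/0.9 = 55.6 to 50/0.7 = 71.4 athletes before any dropout, and the upper end exceeds the oversampling limit of 60 in section 2.4.
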